## Methods

### Study Design

This study is a pilot feasibility trial with a parallel design. Eligible participants will be randomly assigned to either an intervention group (IG) or a waitlist control group (WCG), with both arms delivered online and in group format. A WCG was included to ensure that all interested participants would have access to the intervention offered. This project was prospectively registered with the Australian New Zealand Clinical Trials Registry (ANZCTR12624000460505p) on March 26, 2024 (universal trial number U1111-1305-9340).

The pilot trial will be conducted entirely online using the videoconferencing software Zoom. Participants will be sent a password-protected URL to enter the videoconferencing room.

### Participants

The inclusion criteria were as follows:

Women residing in a catchment area in Northern NSW, Australia, of predominantly rural towns spanning 131,785 km, with an estimated population of 962,390 residents as of 2021.Up to 6 months postpartum.Aged 18 years and above.Proficient comprehension of spoken and written English.Subjectively reporting having had a traumatic birth experience with their most recent birth.Having had a live birth with a gestation of at least 34+ completed weeks. (Births after 34 weeks of gestation are considered late preterm births, and infants may or may not require intensive care. Births prior to this gestation would likely require infants to be hospitalized and remain in intensive care and, therefore, would constitute a specific type of trauma. Such participants would likely benefit from a more homogenous group for increased group cohesion and support.)

The exclusion criteria were as follows:

Women residing outside of the defined catchment area described earlier (Hunter New England Local Health District, NSW, Australia).Nulliparous, pregnant, or more than 6 months postpartum.Under 18 years of age.Not proficient in English.Do not subjectively report having had a traumatic birth experience with their most recent birth.Most recent delivery involving a still birth or a live birth with a gestation of under 34 weeks.Endorsing item 10 on the Edinburgh Postnatal Depression Scale (EPDS; pertaining to suicide risk) or have a total score of more than 13.Having serious mental health concerns that impinge on their ability to provide informed consent (eg, an intense mood or psychotic episode associated with bipolar disorder or schizophrenia).

### Sample Size

The study aimed to recruit 16 participants, which was deemed feasible within the project’s funding budget and timelines and is within the recommended size for group-based teletherapy [41]. As a pilot feasibility and acceptability study, should the study be deemed feasible and acceptable, the study findings may help inform estimates for sample size calculation for a larger trial. Consequently, no formal power calculation was performed for this study.

### Procedure

#### Recruitment

Recruitment took place in July and August 2024 and was completed by the start of September 2024. Participants were recruited through the following:

Midwives and lactation consultants in public and private health care systems who aid postpartum mothers in recovery and breastfeeding.Child and family health nurses who provide free health and developmental checks on growth and development throughout infancy and early childhood. These nurses are also responsible for organizing local mothers’ groups for first-time mothers within a region.Perinatal Infant Mental Health Services (PIMHS), a free mental health service for women up to 2 years postpartum.Local referral hospitals (Armidale and Glenn Innes), who put the recruitment flyers in the personal health record books given to parents of all newborns born within that recruitment period.General practitioner obstetricians providing postpartum checks.Targeted advertising on social media (Facebook).Australian Facebook groups on birth trauma, breastfeeding, etc.Pamphlets with information about the study given to health care providers, including a QR code linking to an expression-of-interest survey.

### Ethical Considerations

This study will be conducted in compliance with all stipulations of this protocol, the conditions of the University of New England Human Research Ethics Committee approval (approval number HE24-054, valid till June 1, 2025), with site-specific approval granted to recruit from Hunter New England Health sites in the towns of Armidale and Glenn Innes; the National Health and Medical Research Council (NHMRC) National Statement on Ethical Conduct in Human Research; and the Australian Code for the Responsible Conduct of Research. The SPIRIT (Standard Protocol Items: Recommendations for Interventional Trials) 2013 checklist was followed when writing this protocol [42].

Potential participants who expressed interest were emailed a detailed information sheet by the research assistant and then invited to a pretreatment session. There was at least a week’s duration between receiving the information sheet and the pretreatment session for potential participants to consider participating. The pretreatment session included an introduction to the chief investigator (CI; author CS), who delivered the intervention and who presented screening questions to determine participant eligibility. The scope of the group therapy and guidelines for participation were explained (eg, telehealth etiquette, the need to be respectful, maintaining confidentiality of other group members, and distress management within sessions). At each individual pretreatment telehealth session, the information sheet was presented again, and participants got an opportunity to ask questions and clarify concerns, leading to the informed consent process. The clinician then gathered personal contact information and emergency contact details from the participants and explained the circumstances in which they would be used (ie, a participant leaves a group session abruptly, and one of the psychologists on the research team needs to do a telehealth welfare check to ensure safety). If deemed eligible, participants then signed the informed consent form, which could be done via an e-signature and sent as a file attachment within the password-protected Zoom Meeting or via email. The pretreatment session concluded with an assessment of the participants’ preferences for the session day and time. Additionally, participants also provided online implied consent before completing the pretest survey. Participants had the right to withdraw at any point without needing to provide a reason. Their identity was only known to the CI (CS) and the research assistant (author HM) to safeguard their privacy. All participants were remunerated with gift vouchers at designated intervals (to a total of AU $200, or ~US $130 at an exchange rate of AU $1=US $0.65, per participant) across the intervention to promote retention.

All data collected will be electronic and kept on the University of New England’s (UNE) centrally managed cloud server, as well as on a password-protected computer. Only the research team will have access to the data. All audio/video files recording the sessions will be deleted upon completion of the transcription process. Quantitative and qualitative data will be deidentified using numerical identifiers. The deidentified data will be stored in the UNE’s online research repository indefinitely and can be made available upon reasonable request.

### Allocation and Concealment

This pilot trial included an IG (who received the intervention immediately after recruitment) and a WCG (who were allocated to a waitlist during the same observation period as the intervention. Although there were no restrictions on outside care for the WCG, no intervention or support was actively offered to these participants. HM monitored the mental health of participants in the WCG (across the outcome measures administered at various timepoints; see Table 1) and alerted the team to any observed deterioration. A recent pilot feasibility trial conducted in Australia noted that people typically wait 6 months or longer to access mental health services [43]. Once the study with the IG concluded, the WCG received the full intervention, which involved a wait time of 6 weeks, significantly less than the typical waitlist.

A randomization sequence in alternating block sizes of 4 and 6 was generated from an online sequence generator by author PJT. The randomization sequence was revealed to the research assistant (HM) and only after completion of the baseline and eligibility measures. At that time, the research assistant informed participants of the intervention start date based on their allocation to either the IG or the WCG.

**Table 1 table1:** Data collection timeline.

Measure	IG^a^ timepoints					WCG^b^ timepoints			
	T1^c^	T2^d^	T3^e^	T4^f^	T1		T2	T3	T4
City BiTS^g^	X^h^	X	X	—^i^	X		X	X	X
EPDS^j^	X	X	X	—	X		X	X	X
PASS^k^	X	X	X	—	X		X	X	X
GCS^l^	—	—	X	—	—		—	—	X
CSQ-8^m^	—	—	X	—	—		—	—	X

^a^IG: intervention group.

^b^WCG: waitlist control group.

^c^T1: prior to session 1 for the IG.

^d^T2: after session 3 for the IG.

^e^T3: after session 6 for the IG.

^f^T4: after session 6 for the WCG.

^g^City BiTS: City Birth Trauma Scale.

^h^X: applicable.

^i^Not applicable.

^j^EPDS: Edinburgh Postnatal Depression Scale.

^k^PASS: Perinatal Anxiety Screening Scale.

^l^GCS: Group Cohesiveness Scale.

^m^CSQ-8: Client Satisfaction Questionnaire.

#### Blinding

Participants were blinded to whether they were in the IG or the WCG. The CI was not involved in the randomization sequencing, nor in communicating intervention start dates to participants, depending on their group membership. However, as the CI was the clinician delivering the telehealth intervention, this was partial blinding. Participants filled in the measures at pre-, mid-, and postintervention timepoints using a unique identifier (generated by HM), so the survey data collected will be anonymous to the statistician.

Pre- (baseline), mid-, and postintervention measures were administered to the IG and WCG according to the schedule depicted in Table 1. The group-based intervention was conducted via telehealth to assess the feasibility and acceptability of a program that is likely to be cost-effective and accessible. The telehealth platform used in this study was a Zoom Conference Room, which was password-protected, so only individuals with the password (ie, study participants who met the eligibility criteria) were able to join in. For added security, all participants were sent two separate modes of communication, one with the Zoom Meeting link and another with the password to this meeting. Email reminders on the 2 days preceding each scheduled session were sent out to all participants. All sessions were recorded with informed consent. These were then transcribed verbatim for qualitative analyses to identify the key themes of healing from traumatic birth experiences.

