**Figure 1 figure1:**
[figure not shown]
Flowchart of the pilot trial procedure. IG: intervention group; WCG: waitlist control group.

To determine treatment acceptability, GCS-7 and CSQ-8 scores will be totaled for each participant, and a range of scores will be examined, including the central tendency score for each group. Higher scores will indicate greater treatment acceptability on both measures. Treatment feasibility will be determined by using attendance and retention metrics, with a threshold of 70% established as the criterion for feasibility drawn from recent research on virtual psychotherapy groups for postpartum mothers [24]. This threshold will apply to both individual participant attendance across all six sessions and overall retention, as measured by completion of postintervention measures across both groups. These predetermined benchmarks will provide clear criteria for determining whether the intervention warrants investigation in a larger trial.

The mental health outcome measures (EPDS, PASS, and City BiTS) will be scored according to the developer instructions. The last observation carried forward (LOCF) approach will be used to deal with any missing values, which involves replacing each missing value of a participant with the last observed value for that participant. The LOCF was chosen for its simplicity and frequent use in clinical trials [58]. As this is predominantly a feasibility and acceptability pilot study whose sample size is insufficiently powered to demonstrate statistically significant treatment effects, the LOCF was chosen over other more complex imputation methods that may not offer substantial benefits at this early stage. The average scores will be compared across the IG (who had these measures administered prior to, during, and after the intervention) and the WCG (who completed measures while they were on the waitlist, as well as after they received the intervention).

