Third, the CI (CS) of this research project also delivered the intervention, given the resource constraints and need for a qualified professional to implement the intervention. To mitigate potential bias, CS was blinded to the random assignment of participants to the IG and the WCG; the research assistant (HM) handled all participant communication with respect to group allocation and the administration of outcome measures; and the coauthor (PT), who was not involved in the intervention delivery, will conduct the statistical data analysis.

Finally, our study does not involve long-term follow-ups beyond the intervention period, which limits our understanding of sustained effects of the intervention. This extended follow-up was not included in the study design, as the primary aims of the study were to assess feasibility, acceptability, and immediate impacts on mental health measures. However, future research with larger samples would benefit from including follow-ups a few weeks or months after the intervention to determine whether any changes in symptoms were sustained.

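### The article calls participants blinded, but each woman knew whether she was being treated when she rated her symptoms; the chief investigator's blinding could last only until the first session

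*Protocol article*

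**What the plan says.** **Participants.** The Blinding section states, with no qualification, "Participants were blinded to whether they were in the IG or the WCG". Allocation and Concealment says that, after baseline and eligibility measures, "the research assistant informed participants of the intervention start date based on their allocation to either the IG or the WCG". Of the waitlist arm it says "no intervention or support was actively offered to these participants", and that this arm later received the full intervention, "which involved a wait time of 6 weeks". The text below Figure 1 describes the waitlist arm as those "who completed measures while they were on the waitlist, as well as after they received the intervention".

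**Chief investigator.** Study Limitations and Future Directions acknowledges that the chief investigator delivered the intervention. As the first of three mitigations it says that the chief investigator "was blinded to the random assignment of participants to the IG and the WCG". The Blinding section says that the chief investigator took no part in the sequence or in communicating start dates, and calls the arrangement partial blinding because the chief investigator was the treating clinician. The Conclusion lists partial blinding among the limitations.

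**Outcomes.** The Outcomes section describes the EPDS, PASS and City BiTS as self-report questionnaires. Under Quantitative Data they are compared between arms at α<.05, and the mean changes and effect sizes are meant to inform a larger trial.

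**The concern.** With self-reported scales the participant is the outcome assessor. If she knows that she is in treatment, or that she is still waiting for it, her expectations can enter her ratings and so the between-arm difference. A waitlist design is a legitimate choice for a pilot, but it cannot blind participants to whether they are being treated.

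Two things are at stake. A reader or risk-of-bias assessor who takes the Blinding section at face value would record a participant-blinded trial, which this was not. And a team that plans the larger trial from these effect sizes would not be warned that they may contain an expectancy component. Separately, an undated statement that the treating clinician was blind to assignment credits the design with a protection that it had only before treatment began.

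**Working it through.** No formula applies, and the article gives no figure to reproduce on this point. The check sets the statements side by side.

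**Participants, in time order**

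1. *T1.* Allocation was disclosed only after baseline and eligibility measures were complete. Baseline ratings were therefore made without knowledge of arm. This is allocation concealment, and it holds.
2. *Notification.* Each woman was told a start date that followed from her arm. The intervention group started immediately; the waitlist arm started after 6 weeks.
3. *T2.* The notes to Table 1 place T2 after session 3 of the intervention group. Sessions attended under the plan: up to three in the intervention group, none in the waitlist arm.
4. *T3.* Table 1 places T3 after session 6 of the intervention group. Sessions: up to six against none. The waitlist arm received the programme only once the intervention group had finished; the Abstract dates these periods as September to October 2024 and from mid-October 2024.
5. *T4.* Waitlist arm only, after its own treatment, so it is not part of the treated-versus-waiting comparison.

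The randomised comparison therefore has two post-baseline timepoints and three symptom scales: 2 × 3 = 6 ratings per woman. All six were due after she had been told her start date and after sessions had begun in one arm and not in the other. None could be made blind to treatment status.

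**Chief investigator, in time order**

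1. Before allocation, the chief investigator held the individual pretreatment sessions, screened for eligibility and knew participants' identities (Ethical Considerations). Not knowing the assignment at this stage was possible and useful.
2. At the first intervention-group session, the chief investigator met that group as its clinician. The women present were the intervention group, and the remaining randomised women were the waitlist arm. With 9 women randomised, 4 and 5 per arm (Abstract), this needs no further disclosure.
3. From then on, blindness to assignment was not possible.

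**Does the existing caveat repair this?** In the Blinding section the phrase partial blinding is tied to the chief investigator's role as clinician. The Conclusion repeats it without saying whom it covers. Neither place withdraws or limits the statement about participants, and the limitations section still states the chief investigator's blinding without an end point.

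**The case against.** The strongest defence is that the arm label may have been withheld: a woman could know her start date without knowing that it made her a control. That is possible, but it does not rescue the claim. Expectancy depends on knowing whether one is being treated, and attending sessions or attending none shows this plainly.

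A second defence is that the chief investigator's position is already disclosed as partial blinding. This stands in part. On that side the fault is overstatement and inconsistency, not concealment, and blindness during screening and enrolment was a genuine safeguard that should stay in the text.

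A third is that the primary aim is feasibility and acceptability, and that the article admits it is underpowered for symptom effects. This also stands and limits the consequence. It does not make the blinding sentence correct, and the symptom effect sizes are still meant to be carried forward.

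A reader might infer more than the documents support:

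- *That the limitations section uses participant blinding to discount bias.* It does not mention participant blinding. Its mitigations concern the chief investigator's dual role.
- *That every outcome is compromised.* Attendance and retention, judged against 70%, are not symptom self-reports. The GCS and CSQ-8 are self-reported, but each arm completes them after its own treatment, so the treated-versus-waiting contrast does not arise.
- *That the statistician is falsely described as masked.* The article says that survey data are anonymous to the statistician, and that the analyst is someone "who was not involved in the intervention delivery, will conduct the statistical data analysis". Neither claims masking to arm. The initials given for the sequence generator and for the analyst differ, so an overlap of roles cannot be established. Relabelling the arms would also do little, since sizes of 4 and 5 identify them.
- *That alerts about deterioration in waitlisted women unblinded the chief investigator.* No alert is reported, and once sessions began such an alert would reveal nothing new about arm.

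**Conclusion.** The participant-blinding statement is wrong as written: the article's own account of notification, waiting and measurement contradicts it. The statement about the chief investigator is true only up to the first intervention-group session and is overstated without that limit.

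The reach is all three between-arm symptom scales at both post-baseline timepoints. The size of any bias cannot be derived from the document. That it would favour the intervention is plausible for self-reports in a waitlist design, but it is an assumption, not something the document shows. The feasibility criteria are unaffected by the self-report concern. The conclusion rests on reading Table 1 as its notes define it, with T2 and T3 of the waitlist arm falling within the 6-week wait; the text below Figure 1 supports that reading.

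**What to change.** - **Blinding section.** Replace the statement on participants with a description of the trial as open-label for participants and clinician once start dates were notified and sessions began, with allocation concealed until baseline and eligibility measures were complete.
- **Study Limitations and Future Directions.** Limit the chief investigator's blinding to screening and enrolment, before the first intervention-group session. Add as a limitation that between-arm differences and effect sizes on the EPDS, PASS and City BiTS come from participants who knew their treatment status, may include expectancy effects, and should be used with that in mind when a larger trial is planned.
- **Conclusion.** Bring the mention of partial blinding into line with the corrected description.

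The cost is a text correction and a less favourable risk-of-bias description. Both groups were already scheduled and treated according to the Abstract, so nothing in the conduct of the trial can or need change. No new data or analysis is required.

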### Intervention Details

The intervention was a group-based early intervention incorporating techniques and ideas from narrative therapy, roughly based on a modified version of the six-session trauma narrative recovery model developed by Lane and Lane [44]. The CI and one of the coauthors (HF) reviewed existing group-based and narrative-informed trauma-based interventions [40,44] and outlined each of the six sessions. A detailed treatment guide is freely available on an online repository for reproducibility of this intervention [45]. Each session ranged from 60 to 120 minutes; a large time range was deliberately proposed to enable participants to take breaks in the session, as needed, to attend to the needs of their babies (eg, a feed, nappy change). The intervention was conducted via a password-protected Zoom Conference Room. Table 2 provides an overview and brief description of each of the six sessions.

**Table 2 table2:** Overview of the six sessions of the intervention.

Session number	Title	Description
1	Introduction and Psychoeducation	The first session introduces group members, recaps group guidelines, provides psychoeducation on birth trauma, and encourages reflection on personal experiences and coping strategies.
2	Sharing Birth Stories and Narrative Techniques	Participants commence sharing birth stories, with the clinician facilitating externalizing language use and implementing the “outsider witnesses” technique to enrich narratives.
3	Sharing Birth Stories and Narrative Techniques	Birth story sharing continues, focusing on externalizing problems and identifying unique outcomes in participants’ narratives.
4	Sharing Birth Stories and Narrative Techniques	This is the final session of birth story sharing, guiding participants to retell their stories with new perspectives and identified unique outcomes.
5	Reflection and Reauthoring	Participants reflect on shared experiences, rewrite or redraw their birth stories with new insights, and plan for the final session.
6	Integration and Closure	The group reflects on changes and emotional shifts, explores future directions, revises personal definitions, and completes a finishing ritual.

The designed intervention was carefully reviewed by an advisory group that consisted of a perinatal clinical psychologist, a narrative therapy clinician (experienced in working with women and trauma), a midwife, a doula (with lived experience from several years prior), and a person with recent lived experience. The group met twice (June and July 2024) and provided recommendations to modify the proposed intervention. Some of these recommendations were suggestions around the language used with participants (eg, changing the commonly used term “group rules” in group therapy to “group guidelines” to make it less authoritative and more collaborative), as well as activities participants could engage in during specific sessions (eg, ideas for “finishing rituals” to commemorate the end of the intervention). The advisory group met again on completion of the pilot trial to discuss findings, implications, and future directions.

